## Abstract

**Introduction:**

Shielding aimed to protect those predicted to be at highest risk from COVID-19 and was uniquely implemented in the UK during the COVID-19 pandemic. Clinically extremely vulnerable people identified through algorithms and screening of routine National Health Service (NHS) data were individually and strongly advised to stay at home and strictly self-isolate even from others in their household. This study will generate a logic model of the intervention and evaluate the effects and costs of shielding to inform policy development and delivery during future pandemics.

**Methods and analysis:**

This is a quasiexperimental study undertaken in Wales where records for people who were identified for shielding were already anonymously linked into integrated data systems for public health decision-making. We will: interview policy-makers to understand rationale for shielding advice to inform analysis and interpretation of results; use anonymised individual-level data to select people identified for shielding advice in March 2020 and a matched cohort, from routine electronic health data sources, to compare outcomes; survey a stratified random sample of each group about activities and quality of life at 12 months; use routine and newly collected blood data to assess immunity; interview people who were identified for shielding and their carers and NHS staff who delivered healthcare during shielding, to explore compliance and experiences; collect healthcare resource use data to calculate implementation costs and cost–consequences. Our team includes people who were shielding, who used their experience to help design and deliver this study.

**Ethics and dissemination:**

The study has received approval from the Newcastle North Tyneside 2 Research Ethics Committee (IRAS 295050). We will disseminate results directly to UK government policy-makers, publish in peer-reviewed journals, present at scientific and policy conferences and share accessible summaries of results online and through public and patient networks.

Strengths and limitations of this studyThis research will provide the first population-scale national assessment about effects of shielding on COVID-19 infection rate, mortality, serious illness, use of National Health Service resources, health-related quality of life and behaviour.In this study, we will develop a logic model for shielding, providing the first summary of the rationale for this internationally unique and untested public health intervention and underpinning interpretation and contextualisation of our study findings.This study will use mixed methods to understand processes, effects and costs of shielding at national and individual level, including assessment of impact of immunological status on outcomes.The primary limitation of the EVITE Immunity study is construction of our matched cohort; we will undertake validation checks to understand differences between groups and allow appropriate adjustments for these in our statistical analysis plan.The development of the EVITE Immunity study has involved people with direct experience of shielding from the outset, with public contributors represented across all aspects of the study, reflecting strong views that evidence about effects of shielding is needed.

## Introduction

Shielding was introduced early during the COVID-19 pandemic across the UK. It was intended to protect those thought to be at highest risk of serious harm should they catch COVID-19 because of pre-existing conditions such as cancer or treatment such as immunosuppressive medications. It became apparent at an early stage of the pandemic that the virus was disproportionately affecting some parts of the general population, including older people^1^ and patients with pre-existing conditions such as cardiovascular disease, respiratory disease and cancer.^2 3^ A cohort study of over 17 million primary care records in England^4^ confirmed the association between diagnoses such as diabetes and asthma and risk of death from COVID-19 and also highlighted the risks associated with deprivation, old age and being male and black or South Asian.

In response to increasing transmission and deaths from COVID-19, governments across the UK nations developed methods to identify people thought to be most vulnerable to COVID-19 infection, hospital and intensive care unit (ICU) admissions, serious illness or death.^5–8^ These people were selected for advice to shield, before and in addition to more general lockdown measures introduced across the population. In March and April 2020, Public Health England and Public Health Wales advised individuals by letter, text or phone call to strictly self-isolate, even from people within the same home, for a period of 12–16 weeks. Support such as food parcels, prescription delivery and priority supermarket shopping slots were provided and individuals were eligible for Statutory Sick Pay.^6 7^ Shielding along with other lockdown restrictions, eased temporarily from late summer 2020 and was then reinstated shortly before Christmas 2020, with some variation by and within nation, until spring 2021.

Shielding aimed to protect those judged to be at highest risk of serious harm should they become infected with COVID-19.^5^ The mechanism for avoiding harm was to avoid infection. Clinically extremely vulnerable (CEV) patients with diagnoses including cancer, serious heart conditions, respiratory problems and receiving certain treatments such as transplants and immunosuppressant medications were identified through algorithms and individual clinical screening methods from routine national and local National Health Service (NHS) data sources.^6–8^ Following a refinement of the medical criteria for shielding in May 2020,^9^ the shielding population increased. In England, it was estimated to be 2.2 million and in Wales 133 000 people at July 2020.^10 11^ Shielding in the UK cost £308 million to deliver in the first 4 months.^12^

Shielding is a new intervention, uniquely used in the UK during the 2020 pandemic without prior evidence of effects on health outcomes or behaviour including intended and unintended consequences.^12–16^ The WHO recognises that some people are at higher risk than others from COVID-19, but states that ‘all must act to prevent community spread’.^17^ It encouraged measures—including physical distancing, handwashing and stay-at-home advice—to limit transmission and protect populations to ensure that health services can sustain increased demand for patient care and treatment.

Evidence is now emerging of effects of shielding on: physical and mental health; well-being and quality of life including social isolation, loneliness and anxiety; access to medical care.^18–21^ Higher COVID-19 rates among people who shielded are also reported.^22 23^ There may be additional secondary effects on physical and mental health, across the shielded population or in subgroups such as the very elderly, people in different clinical condition groups and ethnic minorities. Questions remain about whether the screening process, which involved complex stratification based on modelling to account for ethnicity, deprivation and comorbidities, was the most appropriate approach.^5^

There is a pressing need for rigorous population level evidence to build on early findings from the small-scale studies undertaken so far. It is well known that healthcare interventions do not always achieve intended effects.^24 25^ High-quality evidence about effects of shielding advice on COVID-19 infection rate, mortality, serious illness, use of NHS resources, health-related quality of life and behaviour is therefore urgently required to inform policy and practice throughout this and any future pandemic.

We describe our protocol to evaluate the effects and costs of shielding in Wales where we will extend existing data linkage to COVID-19 diagnosis and antibody (serology) laboratory results, adopting a quasiexperimental matched cohort linked data study design to answer our research questions. As the shielding policy in Wales broadly replicated the policy in the rest of the UK, evidence from this evaluation will inform policy development and delivery in England as well as the devolved nations.

### Study aim

To measure effects and costs of shielding to protect members of the general population at highest risk of serious illness or death from COVID-19 in Wales.

### Objectives

Capture the rationale for UK shielding.Assess effects of shielding in the general population and subgroups in terms of deaths, hospitalisations, safety and self-reported health.Assess the infection levels and immunity within the shielded and control populations as a whole.Explore behaviour, adherence and safety concerns relating to shielding.Assess the costs of the shielding intervention against its consequences.Understand the experiences and views of healthcare providers in relation to the shielding intervention and perceived effects, including healthcare associated harms.

## Methods and analysis

See table 1 for an overview of objectives, methods and outputs.

**Table 1 T1:** Summary of methods and outputs against study objectives

Objective	Method	Output
1. Capture rationale for UK shielding.	Interviews with policy-makers.	Logic model to describe components, outcomes and mechanisms of shielding.
2. Assess effects of shielding in the general population and subgroups in terms of deaths, hospitalisations, safety and self-reported health.	Comparison of anonymised routine data between shielded population and comparator group.	Comparative outcomes for shielded and matched non-shielded people: COVID-19 tests, PCR-confirmed infections and deaths. All-cause mortality. Emergency department attendances, emergency hospital admissions, days spent in hospital, ICU admissions and days spent in ICU.
	Questionnaire to stratified random sample of intervention and control groups.	Self-reported health-related quality of life, anxiety, depression and loneliness.
3. Assess the infection and immunity within the shielded and control populations as a whole.	Analysis of routine records of blood tests in shielded population. Analysis of blood samples from stratified random subsample of intervention and control groups.	Detailed analysis of COVID-19 antigen and antibody test results within the shielded and comparator populations, to understand: Effects of shielding on infection and immunity across the population and for clinical subgroups including cancer. Impact of immunological status on outcomes in the shielded and non-shielded population.
4. Explore behaviour, adherence and safety concerns relating to shielding.	Interviews with 40 individuals and carers/household members who were shielded.	Experiences of shielded people and their carers or household members during the COVID-19 lockdown, including behaviour, emotional effects and safety concerns.
5. Assess costs of the shielding intervention against its consequences.	Investigation of costs and cost–consequences of managing and delivering shielding.	Costs of intervention implementation and subsequent healthcare resource use compared with consequences and outcomes, net monetary benefit.
6. Understand the experiences and views of healthcare providers in relation to the shielding intervention and perceived effects, including healthcare associated harms.	Interviews with 30 community-based health professionals.	Experiences of clinicians delivering care to shielded population during pandemic.

ICU, intensive care unit.

### Design

Quasiexperimental evaluation.

### Participant identification and participation (objectives 2–5)

Eligible participants will include those identified as CEV in Wales between March and May 2020 and who were advised to shield (shielded cohort). We will use individual-level population-scale anonymised data within the Secure Anonymised Information Linkage (SAIL) Databank to identify those shielded and their linked Electronic Health Records (EHR) from routinely collected NHS data sources, Office for National Statistics data and other health and administrative data, including the Wales Multimorbidity Cohort COVID-19 extension, under existing Information Governance Review Panel (IGRP) approvals.^26^ We will also identify a cohort to match those identified for shielding with partners in Digital Health and Care Wales (DHCW), through cohort ‘propensity’ matching variables including age, sex and historic health service utilisation. We will create a stratified random sample from each of the two cohorts for questionnaire distribution and blood sample collection. Prospectively collected data from questionnaires and bloods will be linked back into the SAIL Databank for anonymised linkage. Figure 1 describes data flow. Figure 2 describes recruitment and participation.

**Figure 1 F1:**
[figure not shown]
Data flow visualisation.

**Figure 2 F2:**
[figure not shown]
Study participant recruitment flow chart.

### Intervention

Individuals on the Shielded Persons List identified as CEV were sent advice (table 2), by letter (dated 24 March 2020) email or text, to stay at home for 12 weeks and ‘do not go out at all’ plus to minimise contact with anyone in the same household or visiting to provide care, ‘even friends and family’.^27^ Correspondence after the first 12-week shielding period reflected an easing, then reinstatement, then more easing.^28–31^

**Table 2 T2:** Shielding advice given to clinically extremely vulnerable (CEV) people

Key points	Do not leave the house to go to work or to see other people
	Avoid being in the same room as another person
	Keep three steps away from another person in the home
	Avoid sharing kitchen, bathroom or bedroom facilities with others in the home
	Eat meals separately from other household members
	Be aware that hospital appointments and treatment may be postponed or cancelled
Support	Letters included details of available support, including how to obtain food, prescriptions and other information
Repeat advice	Letters were sent to CEV people throughout the pandemic which updated current advice.
	Correspondence after the first 12-week shielding period reflected an easing of some of the above points until January 2021 when shielding advice was reinstated. Advice remained, with some amendments, until August 2021. Shielding officially ended in March 2022.

### Methods for each objective

#### Objective 1: rationale for UK shielding

We will conduct virtual interviews and focus groups with senior policy-makers and clinicians from Public Health and Chief Medical Officers’ teams in Wales and England. We will encourage participants to consider the aim of the shielding policy, components of the intervention, the way it was intended to work and any perceived risks or unintended consequences of shielding. We will invite comments from participants on a draft logic model, including: components of the intervention; mechanisms for change (how the intervention was expected to work); expected outcomes and impacts, including harms. The draft logic model was prepared by the study team based on published information. We will record and transcribe interviews, with participants’ consent, and will use data to refine and agree a logic model^32 33^ to guide interpretation of study findings.

#### Objective 2: effectiveness of shielding

We will create a matched electronic cohort and compare demographics and clinical characteristics to understand differences between the two groups; it will not be possible to achieve a perfect match, but characterisation of differences, incorporated into our statistical analysis plan, will allow appropriate adjustments when answering our research questions. We know that those warranting shielding will have higher utilisation rates. The rationale for matching on healthcare utilisation is to identify people who should have been shielding (but were missed due to initial selection of conditions based on prioritisation for influenza vaccination and/or administrative error) who can be matched on propensity, to create as similar as possible a comparator group (in the absence of randomisation) and use a difference in difference approach to estimate effectiveness, comparing pre intervention and post intervention health service utilisation rates.

We will use anonymised individual-level linked routinely collected anonymised EHR data to compare outcomes between the two cohorts—COVID-19 infections, deaths, hospitalisations, immunity status, safety and costs up to 12 months. Inclusion of approximately 120 000 people in each cohort—from date of their addition to the shielding list between 23 March and 31 December 2020; and from 23 March 2020 for the matched control groups: with follow-up of outcomes up to 1 year—gives ample power to detect small differences (standardised statistical effects as small as 0.05, 90% power, 5% significance) in outcomes between groups and between most subgroups. For instance, 3%–5% of each cohort will be recorded as belonging to a black, Asian or other minority ethnic group, allowing comparison of outcomes between up to 6000 people per subcohort; larger numbers will be included in clinical subgroups such as cancer, heart disease, diabetes. We recognise it will not be possible to completely mirror the shielded group in our matched cohort. Our statistical analysis plan will incorporate ways of characterising differences and making appropriate adjustments.We will examine self-reported outcomes at 12 months. We will distribute 1333 postal questionnaires (with online response option) (online supplemental appendix 1) to a stratified random sample in each of the shielded and non-shielded (matched) cohorts to achieve 533 responses in each. Questionnaires will include: the health-related quality-of-life measure (SF12);^34^ measures of common mental disorders, anxiety and depression (PHQ9, GAD7);^35 36^ safety concerns and behaviour during COVID-19 lockdown (staying home, isolating—including within home). Our sample size is sufficient to detect an average difference of 2.5 in SF12 component scores (standardised statistical effect 0.2, 90% power, 5% significance). Our Wales NHS partners, who hold contact details of individuals, will send the questionnaires and assign each an anonymised ID number. This will ensure that the research team has no identifying information about participants at any stage of the evaluation.

10.1136/bmjopen-2021-059813.supp1Supplementary data

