#### Objective 2: effectiveness of shielding

We will analyse quantitative data following ‘intention to treat’ analysis principles. Our detailed statistical analysis plan, compliant with Swansea Trials Unit’s Standard Operating Procedure,^42^ will cover: descriptive summaries of study data and thematic categorisation; formal comparison of outcomes, adjusted for case mix and potential confounding factors; statistical modelling strategy underpinning comparisons, including conventions for dealing with missing data, selection of confounders; reporting of analyses. Modelling will use generalised linear and survival multilevel models for events, counts and time to events. Entry dates are based on the date identified as CEV (shielded cohort) or 20 March 2020 (matched cohort); 12-month follow-up data will be censored by death, or known date of migration from Wales.

There was considerable spatial as well as temporal variation in the (estimated) R number across Wales during our study window, with little detailed data on the accuracy of these estimates. Although difficult to justify incorporation of such estimates into formal models, we will use what is known to inform discussion of our results. We will assess if available anonymised residential identifiers allow creation of usable household/residential clusters, and, if so, whether extension to include clustering improves our models. We will consider further use of care home residence identifiers and critical care and hospital in-patient spells in defining potential explanatory covariates and factors for inclusion in models.

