### Study design limitations

As the shielding intervention was introduced across all the UK at one timepoint, we are able to carry out a quasiexperimental study only, with no clear historic or concurrent control group. In this circumstance, we acknowledge that any method to identify a matched comparator group is, to some extent, flawed. As entire clinical codes were allocated to the CEV (shielded) group, we intend to match as well as we can, from routine data sources, by age, sex and health service utilisation in the year prior to introduction of the shielding policy. We will then compare clinical, demographic and socioeconomic characteristics of our two groups and adjust for differences in our analysis. Without any group for comparison of outcomes it is difficult to draw any conclusions related to the benefits, harms and costs of the shielding policy. We have, therefore, selected this study design as the best available for this study.

The study was designed before widespread availability of vaccinations. We do not intend to include this variable in our data collection and analyses; so many variations in timing, vaccination delivered, number of vaccinations and boosters means this analysis is outside the scope of the current study.

Although not all those included in the shielding intervention will have received letters or complied with advice, and some people in the non-shielding cohort may have strictly self-isolated, we are following principles of analysis by intention to treat or treatment allocated^47^ as this is most suited to a pragmatic evaluation context where study findings relate to how the intervention was implemented, not just how it was intended.

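### Shielded people enter follow-up at their own listing date and controls on one fixed March 2020 date, so the two cohorts' 12-month windows cover different parts of the pandemic

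*Protocol article*

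**What the plan says.** The Methods text for Objective 2 sets the start of follow-up as the "date of their addition to the shielding list between 23 March and 31 December 2020; and from 23 March 2020 for the matched control" cohort. Each person's outcomes are then counted for at most one year. The Analysis text for Objective 2 keeps the asymmetry but gives a different control date: "Entry dates are based on the date identified as CEV (shielded cohort) or 20 March 2020 (matched cohort"). It adds that "12-month follow-up data will be censored by death, or known date of migration from Wales". It states no common calendar end date.

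Matching is described under Study design limitations as being "by age, sex and health service utilisation in the year prior to introduction of the shielding policy". Listing date is not among the matching variables, and no section gives a control the index date of its match.

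The shielded entry window is given three ways: March 2020 in the Abstract, March to May 2020 under Participant identification and participation, and up to 31 December 2020 in the Methods for Objective 2.

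On changes over time, the Analysis section accepts that estimated R varied considerably across Wales during the study window and says of those estimates: "Although difficult to justify incorporation of such estimates into formal models, we will use what is known to inform discussion of our results". Table 2 records that shielding advice was eased after the first 12 weeks, reinstated in January 2021 and kept, with amendments, until August 2021. Study design limitations says vaccination will be neither collected nor analysed.

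**The concern.** A matched cohort comparison needs the two members of a pair to start being at risk at the same moment. Here the start date is nearly determined by the arm. Someone listed well after March 2020 contributes no spring 2020 follow-up, which every control contributes. They do contribute 2021 follow-up that no control contributes. Any change over calendar time in infection risk, service use, advice or vaccination is then mixed with the effect of shielding. Adjusting for characteristics at entry does not separate the two.

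Selection adds to this. The plan looks for controls among people who should have been listed but were missed. Such a person who survives to a later listing can enter the shielded cohort, while one who dies first can only be a control. Early control deaths therefore have no counterpart among late-listed people.

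The comparisons at stake are those built from routine data: deaths, infections, admissions, attendances, days in hospital and intensive care, the difference-in-difference estimate of utilisation, and the Objective 5 resource costs. With about 120 000 people per cohort, random error is small, so a systematic difference of this kind is what would decide the answer.

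**Working it through.** **The plan's own figure.** The only computable figure in the sentence that sets the entry dates is the power statement. For a standardised effect of 0.05, 90% power and two-sided 5%, n per group = 2 × (1.960 + 1.282)² / 0.05² = 2 × 10.507 / 0.0025 ≈ 8406. With 120 000 per group power exceeds 0.999, so the statement of ample power for the whole cohorts reproduces. The point here does not depend on it.

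**Calendar overlap.** Inputs: control start 23 March 2020 (Methods, Objective 2) or 20 March 2020 (Analysis, Objective 2); 12 months of follow-up taken as 365 days; shielded entry at the limits the document gives.

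Offset = shielded entry date − control entry date. Shared days = 365 − offset.

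| Shielded entry | Source of limit | Offset from 23 March | Shared days | Offset from 20 March | Shared days |
|---|---|---|---|---|---|
| 23 March 2020 | Methods, earliest | 0 | 365 (100%) | 3 | 362 (99.2%) |
| 31 May 2020 | Participant identification | 69 | 296 (81.1%) | 72 | 293 (80.3%) |
| 31 July 2020 | intermediate illustration | 130 | 235 (64.4%) | 133 | 232 (63.6%) |
| 31 December 2020 | Methods, latest | 283 | 82 (22.5%) | 286 | 79 (21.6%) |

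All control windows close by 23 March 2021. A window opened on 31 December 2020 runs to 31 December 2021, so 283 of its 365 days have no control under observation. The three-day difference between the two control dates hardly changes these figures. It is a wording conflict, not a source of bias worth measuring.

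**Can the bias be sized?** To first order, the apparent relative reduction in 12-month events with no true effect is

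p × (f − g),

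where p is the share of shielded people listed after the early period, f is the share of the controls' 12-month events falling in the early period that late-listed people miss, and g is the events in the later period that replaces it, on the same scale. The documents give none of the three.

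- Assume p = 10–20% and f = 30–40%. If g = 0, the result is 0.10 × 0.30 = 3% to 0.20 × 0.40 = 8% in favour of shielding.
- If g = f, the result is 0.
- If g exceeds f, the sign reverses. With p = 20%, f = 30% and g = 40%, it is 0.20 × (0.30 − 0.40) = −2%, an apparent excess.

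This covers calendar time only; survival to listing is a further component. Neither size nor direction follows from the documents.

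**After correction.** If each control takes its match's listing date, the offset is 0 and the overlap is 365 of 365 days for every pair.

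**The case against.** The strongest reply has four parts.

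1. *The 22% describes one extreme entrant.* The eligibility section stops at May 2020. The Introduction puts the Welsh shielding population at 133 000 in July 2020, already above the roughly 120 000 planned. This suggests that late entry may be uncommon. It stands as a limit on size but does not remove the point: the Methods section explicitly admits entry to 31 December, and a May limit still leaves up to 69 days without overlap at the start of the pandemic.

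2. *The time scale is left to the analysis plan.* Survival models on calendar time with delayed entry would bring late-listed people into risk sets only once listed, which handles both calendar risk and survival to listing. This stands for time-to-event outcomes over the shared days. It does not repair 12-month counts, costs or the difference-in-difference comparison, which needs the post-policy period to be the same for both arms if pandemic-wide shocks are to cancel. Nor does it supply controls after their windows close. The entry dates are fixed in the protocol itself.

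3. *Declining to model R is not declining calendar time.* This is correct. A reader might infer that the plan rejects calendar-time adjustment, but it only keeps poorly documented R estimates out of formal models.

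4. *Stronger readings go too far.* A reader might infer a spurious benefit of 3–8% for shielding; that figure gives late-listed people no risk in the period that replaces the missed one. A reader might suppose that late listing usually reflects a new diagnosis; the document mentions only the refined criteria of May 2020, initial selection of conditions and administrative error. A reader might extend the problem to every Objective 2 outcome, but the SF12, PHQ9 and GAD7 are survey scores, not events accumulated over the mismatched windows. None of these three is supported.

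**Conclusion.** The point holds for the routine-data event, count, cost and difference-in-difference comparisons of Objectives 2 and 5. Both the Methods and the Analysis sections set an individual start for shielded people and a common start for controls, so this is a stated rule and not a detail left to another document. Shared follow-up falls to 82 of 365 days (22%) at the latest entry the Methods allow, and to 296 days (81%) at the end of the eligibility section's window.

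That the mismatch matters rests on the protocol's own account that epidemic risk and advice changed over the period, and on its decision not to measure vaccination. The magnitude and sign of the bias remain unknown without the distribution of listing dates and the timing of events. The lack of a stated rule for controls listed later is not counted against a condensed article, but the revised matching rule has to settle it.

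**What to change.** - Give each control the listing date of the shielded person they are matched to as the start of follow-up.
- Require the control to be alive, resident in Wales and not yet listed on that date, and analyse everyone by their status on that date.
- Measure matching utilisation in the 12 months before that date, so both members of a pair are described over the same period.
- Run the time-to-event models on the calendar-time scale, with the baseline hazard stratified by area if useful. This allows for variation in time and place without using R estimates.
- State one entry window for the shielded cohort, reconciling the Abstract (March 2020), the eligibility section (March to May 2020) and the Methods (to 31 December 2020). Remove the conflicting 20 and 23 March control dates.
- Report the distribution of listing dates, so that readers can judge how much the alignment mattered.

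The cost is revised wording and a re-run of the matching on linked data already held, with somewhat more computation. The questionnaire and blood samples are drawn from the matched cohorts. If they have already been drawn, some sampled controls may fall outside the re-matched cohort; those samples can keep the match from which they were taken, with this stated in the report.

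### The ethnic-minority comparison given to illustrate 90% power for a standardised effect of 0.05 has about 56% to 78% power in an unadjusted two-sided test

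*Protocol article*

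**What the plan says.** In the protocol article, Methods for each objective, Objective 2, the linked-data comparison rests on "Inclusion of approximately 120 000 people in each cohort". The article says this gives ample power for small differences, which it specifies as "standardised statistical effects as small as 0.05, 90% power, 5% significance) in outcomes between groups and between most subgroups".

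The next sentence is introduced as an instance of that claim. It takes an ethnic-minority share of 3% to 5% in each cohort and describes the result as "allowing comparison of outcomes between up to 6000 people per subcohort". It then adds that "larger numbers will be included in clinical subgroups such as cancer, heart disease, diabetes", without giving those numbers.

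The article does not say whether the 5% level is one-sided or two-sided. The same section sizes the questionnaire sample at 533 responses per cohort, for a "standardised statistical effect 0.2, 90% power, 5% significance".

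**The concern.** The ethnic-minority comparison is the only subgroup that the article sizes, and it is presented as an example of the power claim. If its own head-count does not deliver the stated power, the example contradicts the sentence it is meant to support.

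This affects how results are read. Subgroup effects are part of Objective 2, and the Introduction names ethnic minorities among the groups that may experience additional effects. A reader who meets a null result in this subgroup could take it as coming from a comparison with 90% power for 0.05, when the true figure is lower.

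**Working it through.** **Inputs from Objective 2 of the article**
- Standardised effect d = 0.05, power 90%, significance 5%.
- About 120 000 people per cohort, so 1:1 comparison.
- Ethnic-minority share 3% to 5%: 0.03 × 120 000 = 3600 and 0.05 × 120 000 = 6000 per cohort. The upper figure matches the article's stated ceiling.

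**Assumptions of this check**
- Two-sided 5%; one-sided is also tried.
- Unadjusted comparison of two independent groups, SD = 1, normal approximation.

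**1. Benchmark on the article's own questionnaire figure**

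n per group = 2 × (1.960 + 1.2816)² / d² = 2 × 10.507 / 0.2² = 526.

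The article plans 533, which gives 90.4% power. The formula and the two-sided reading therefore fit the article's own practice.

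**2. Size needed for d = 0.05**

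- Two-sided: n = 2 × 10.507 / 0.05² = 8406 per group, and 8406 / 120 000 = 7.0% of a cohort.
- One-sided: n = 2 × (1.645 + 1.2816)² / 0.05² ≈ 6852 per group.

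Both exceed the example's ceiling of 6000.

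**3. Power at d = 0.05**

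Power = Φ(0.05 × √(n/2) − z), with z = 1.960 (two-sided) or 1.645 (one-sided).

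| n per cohort | 0.05 × √(n/2) | Two-sided power | One-sided power |
|---|---|---|---|
| 3600 | 2.121 | 56.4% | 68.3% |
| 4800 (4%) | 2.449 | 68.8% | 78.9% |
| 6000 | 2.739 | 78.2% | 86.3% |
| 120 000 | 12.247 | above 99.9% | above 99.9% |

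**4. Effect detectable with 90% power, two-sided**

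d = √(2 × 10.507 / n)
- n = 3600: 0.076
- n = 6000: 0.059
- n = 120 000: 0.013

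**5. Binary outcomes**

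With the effect expressed as Cohen's h = 0.05 and base rates from 1% to 50%, two-sided power is 55.9% to 56.4% at 3600 and 77.7% to 78.2% at 6000. The type of outcome does not change the result.

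**6. Gain from baseline data**

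For a difference-in-difference change score, the SD becomes √(2(1 − ρ)), where ρ is the pre/post correlation. The article gives no ρ, so a range is shown.

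| ρ (assumed) | Power at 3600 | Power at 6000 |
|---|---|---|
| 0.3 | 43% | 64% |
| 0.5 | 56% | 78% |
| 0.7 | 78% | 94% |
| 0.8 | 92% | 99% |

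**The case against.** **The claim covers most subgroups, not all.** This stands. One subgroup below 8406 does not refute it, and clinical subgroups above that size may well satisfy it. Their sizes are not given, so a reader who infers that the subgroup claim as a whole is false goes beyond the document. What remains is that the article picked as its example a subgroup that falls short.

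**The example sentence is only a head-count.** It restates no effect size or power, so this is not a miscalculated figure in that sentence. But it is introduced as an instance of the preceding power claim, and readers will attach 90% and 0.05 to it.

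**The analysis will not be an unadjusted two-group test.** The article plans a difference-in-difference approach for service utilisation and adjusted multilevel models. A correlation of 0.7 would bring 6000 per cohort to 94%, though 3600 would still have only 78%. So 56% to 78% is conditional on no such gain. The article states no correlation, and deaths have no baseline value from which to gain.

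**The comparison might be minority against non-minority people within one cohort.** That gives 84% at 3600 and 97% at 6000. However, the wording "allowing comparison of outcomes between up to 6000 people per subcohort" describes like-sized groups in the shielded and matched cohorts.

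**Nothing in the study changes.** This also stands. Cohort size follows from who was on the shielding list, and the shift in detectable effect is modest.

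**Conclusion.** The point holds in limited form. The stated combination of 90% power and 0.05 is not delivered by the article's own example: power is about 56% at 3600 per cohort and 78% at 6000, and the 90%-power detectable effect is 0.076 to 0.059. This assumes an unadjusted two-sided 5% comparison of shielded with matched ethnic-minority people. One-sided testing does not close the gap.

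Two stronger readings are not supported:
- A reader might infer that 0.05 is also wrong for the full cohorts, because 0.013 is detectable there. Power for 0.05 at 120 000 per cohort exceeds 99.9%, so the statement is true and merely conservative. The article does not present 0.05 as the smallest detectable effect.
- A reader might infer that the subgroup would miss large relative effects on death or intensive care admission. The article gives no event rates, so any such figure would rest on assumed ones.

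Severity is minor to moderate. The error concerns how one subgroup result would be interpreted; the main comparison is unaffected.

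**What to change.** Reword the power sentence in Objective 2, or correct it in the statistical analysis plan:
- Limit the claim of 90% power for 0.05 to the full cohorts and to subgroups of at least about 8400 people per cohort (7%).
- State a detectable effect of about 0.06 to 0.08 for the ethnic-minority comparison. If a better figure is claimed, name the pre/post correlation it assumes and the outcomes to which it applies.
- State that the 5% level is two-sided.

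The cost is a sentence or two, and a less favourable figure for one subgroup. Recruitment, data collection and the main analysis stay as they are.
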